### Objectives

To examine the self-improvement benefits suggested in self-reports, we will assess the measures of personality structure and creativity. Specifically, open-mindedness and the related construct of absorption, as well as divergent and convergent thinking will be measured. Our hypotheses here are that participants will show increased open-mindedness compared to placebo as measured by the Big Five Inventory-2 (BFI-2) [50] and absorption as measured by the Modified Tellegen Absorption Scale (MODTAS) [28, 51], and increased divergent thinking as measured by the Alternate Uses Test (AUT) [35] and convergent thinking as measured by the Remote Associates Task (RAT) [52].

To assess the possible neural mechanisms of these changes, we will use established measures of cortical plasticity and connectivity. We hypothesise that participants who receive LSD will show greater levels of plasticity than placebo, as measured by the LTP and MMN paradigms described by Sumner et al. [53, 54], and will show modification to the connectivity of the DMN as measured by analysis of within- and between-network correlations of node activity during resting-state fMRI.

Because of the early stage of the field, a comprehensive battery of secondary measures will be administered, including mood, cognition, mindfulness, flexibility, peripheral blood mononuclear cell (PBMC) biomarkers, inflammatory cytokines, drug plasma levels, and supplementary creativity, personality, and connectivity measures (see Table 3). Analysis of these secondary measures will be considered exploratory, and reporting of any significant results will reflect the caution necessary in interpreting them appropriately.

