### Statistical analyses and power calculations

Given the novelty of the study, there are no effect sizes on which to base power calculations. The following power sensitivity calculations were performed in G*Power 3.1 [71] using *α* = 0.05, (1-*β*) = 0.8. For independent sample *t* tests where *n* = 80, our trial will be sensitive to the effects where Cohen’s *d* = 0.56. For linear regressions, *r =* 0.37 with *n* = 40 (single group) and *r* = 0.27 with *n* = 80 (combined groups). Dropouts are anticipated; however, due to the novelty of the protocol, the rate cannot be estimated. Dropouts and other instances of missing data will be accounted for in the analysis (see the “Sub-group data analysis and handling missing data” section). In the event that there are more than ten dropouts, an extra randomisation block of participants will be added to the study and the data added to per-protocol analyses.

Questionnaires and creativity tasks will be assessed with linear mixed models with participants modelled as random factors, using baseline measurements as a covariate. Analysis of language-based creativity tasks will additionally include fluency (as measured by the NIH Picture Vocabulary Test) as a covariate. EEG LTP and MMN data will be analysed consistent with Sumner et al. [53, 54]. fMRI data will be analysed for network connectivity, inter-network connectivity, and node-based connectivity, with an additional secondary analysis of seed-based functional connectivity of the left and right amygdala. Daily questionnaire VAS data will be analysed using a linear mixed effects model. Regression analyses of any significant effects will be undertaken with genetic biomarkers, baseline MODTAS scores, change in MODTAS scores, SoS/SoP, and fMRI baseline connectivity of the DMN as predictors. Expectancy effects will be assessed by regression analysis of measure scores to a corresponding construct on a baseline expectancy questionnaire (Table 4). Due to the use of multiple primary outcome measures, the Bonferroni-Holm step-down procedure will be employed to correct for multiple comparisons where appropriate. Secondary measures will be uncorrected but considered as exploratory.

**Table 4 Tab4:** Expectancy items and corresponding measures

Expectancy item	Measures
*Do you expect that microdosing will change how ____ you feel?*	
Angry	Anger VAS
Anxious	Anxiety VAS DASS Anxiety (−) DFlex BFI-2 Negative Emotionality
Calm	Calm VAS

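### The three sensitivity figures (d = 0.56, r = 0.37, r = 0.27) hold only for undeclared one-sided tests, and the d figure leaves out the Holm correction planned for the primary outcomes

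*Protocol article*

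**What the plan says.** All the figures are in the Protocol article, Statistical analyses and power calculations. The calculations were run in G*Power "using *α* = 0.05, (1-*β*) = 0.8". For the group comparison the text reads "For independent sample *t* tests where *n* = 80", and then "our trial will be sensitive to the effects where Cohen’s *d* = 0.56". For regressions the detectable r is "0.37 with *n* = 40 (single group) and *r* = 0.27 with *n* = 80 (combined groups"). Nothing there or elsewhere in the article says whether tests are one- or two-sided.

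Later in the same section, because there are several primary outcomes, "the Bonferroni-Holm step-down procedure will be employed to correct for multiple comparisons where appropriate". Table 3 lists seven primary measures: AUT, BFI-2 open-mindedness, visual LTP, roving MMN, MODTAS, RAT and resting-state fMRI.

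The Objectives section words most primary hypotheses as increases, for example "participants will show increased open-mindedness compared to placebo". The imaging hypothesis differs: participants on LSD "will show modification to the connectivity of the DMN", with no direction given.

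**The concern.** A reader who sees alpha = 0.05 without qualification will take the tests to be two-sided. On that reading none of the three figures is right, and power at each printed effect is about ten percentage points below the stated 80%. A one-sided calculation is possible for the directional hypotheses, but it would have to be declared, and it cannot serve the imaging outcome.

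The second difficulty is internal to the section. The d figure is for a single test at the full 0.05, while the primary outcomes are to be tested under Holm, where a result may have to pass a much smaller threshold. The section says that no prior effect sizes are available, so these figures are the only quantitative account of what 80 participants can show. They should match the tests that will be run.

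**Working it through.** **Inputs.** Alpha 0.05, power 0.80 and n = 80 come from the power section. The 1:1 allocation comes from Study design and gives 40 per group. Sidedness is not given, so both versions were tried.

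**Formulas.**
- Two-sample t test: df = 78, noncentrality δ = d × √(40/2) = d × 4.472.
- Bivariate regression: df = n − 2, δ = √n × r / √(1 − r²), so r = k / √(1 + k²) with k = δ/√n.
- δ is the value at which the noncentral t distribution gives 80% power.

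**Step 1: reproduce the printed figures.**

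| | Critical t | δ for 80% power | Detectable effect | Printed |
|---|---|---|---|---|
| d, one-sided | 1.665 | 2.508 | 2.508/4.472 = 0.561 | 0.56 |
| d, two-sided | 1.991 | 2.837 | 2.837/4.472 = 0.634 | 0.56 |
| r, n = 40, one-sided | 1.686 | 2.532 | 0.372 | 0.37 |
| r, n = 40, two-sided | 2.024 | 2.875 | 0.414 | 0.37 |
| r, n = 80, one-sided | 1.665 | 2.508 | 0.270 | 0.27 |
| r, n = 80, two-sided | 1.991 | 2.837 | 0.302 | 0.27 |

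One-sided testing reproduces all three figures to two decimals. Two-sided testing reproduces none. Other two-sided methods for r are further away: Fisher z gives 0.431 and 0.309, and a random-predictor model gives 0.426 and 0.307. Reading n = 80 as per group gives d = 0.45 two-sided or 0.39 one-sided, so that does not explain 0.56 either.

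**Step 2: power at the printed effects.**
- d = 0.56 (δ = 2.504): 79.9% one-sided, 69.6% two-sided.
- r = 0.37, n = 40 (δ = 2.519): 79.6% one-sided, 69.0% two-sided.
- r = 0.27, n = 80 (δ = 2.508): 80.0% one-sided, 69.8% two-sided.

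**Step 3: Holm, for d only.** Taking m = 7, the smallest p-value is compared with 0.05/7 = 0.00714 and the largest with 0.05.

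| | Last step (0.05) | First step (0.00714) | Power at d = 0.56, first step |
|---|---|---|---|
| Two-sided | 0.63 | 3.616/4.472 = 0.81 | 40% |
| One-sided | 0.56 | 3.356/4.472 = 0.75 | 50% |

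So even if one-sided tests were intended throughout, d = 0.56 holds only at the last, least strict step.

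**Step 4: effect of baseline adjustment (illustration).** With a baseline-to-outcome correlation ρ, the detectable difference in units of the unadjusted SD shrinks by about √(1 − ρ²). The protocol gives no ρ, so the values below are assumptions.
- ρ = 0.5, factor 0.866: two-sided d is 0.634 × 0.866 = 0.55 at 0.05, and 0.809 × 0.866 = 0.70 at the first Holm step.
- ρ = 0.7, factor 0.714: 0.634 × 0.714 = 0.45 at 0.05, and 0.809 × 0.714 = 0.58 at the first Holm step.

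**The case against.** The strongest reply is that nothing was miscalculated. Six of the seven primary hypotheses predict an increase, Table 4 marks expected signs for the expectancy correlations, and one-sided figures suit directional claims. That stands in part: the arithmetic is correct for one-sided tests at 0.05, and two-sided testing should not be presented as what the authors must have meant. It does not remove the point, because the choice is undeclared, the imaging hypothesis has no direction, and one-sided testing leaves d = 0.56 unsupported at every Holm step but the last.

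A reader might go on to infer that the trial is less sensitive than it claims. The documents do not support that. The printed figures are for unadjusted t tests, whereas questionnaires and creativity tasks, which supply four of the seven primaries (BFI-2 open-mindedness, MODTAS, AUT, RAT), are to be analysed with baseline as a covariate. Step 4 shows that a moderate baseline correlation could offset the whole loss from two-sided testing for those outcomes.

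Three further inferences should be resisted:
- **Holm and the r figures.** The correction is tied to the primary outcomes. The regressions are follow-up and expectancy analyses, so only sidedness applies to them.
- **0.81 as the detectable effect.** It is the strict end of a range, and m = 7 is a count from Table 3. Several measures yield more than one score, so the number of tests could be larger.
- **Dropout as a concealed flaw.** The section says openly that the rate cannot be estimated and provides for an extra randomisation block after more than ten dropouts.

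Nor does the article say that 80 was derived from d = 0.56. It calls these sensitivity calculations, within an exploratory framework.

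**Conclusion.** The concern holds as an error in the printed sensitivity figures. It is more than an omitted detail, because the article prints specific numbers that do not follow from its stated inputs on the usual two-sided reading, and the d figure conflicts with the section's own multiplicity plan on either reading. Two-sided, the figures are d = 0.63, r = 0.41 (n = 40) and r = 0.30 (n = 80), with about 70% power at the printed values.

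The sidedness result needs no assumption beyond 40 per group and the standard noncentral t calculation. The Holm range rests on m = 7. What the trial can detect on its baseline-adjusted outcomes cannot be settled from the document, because no baseline correlation is given.

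**What to change.** 1. State whether the tests are one- or two-sided.
2. Make the figures match. Either restate them as two-sided (d = 0.63 at n = 80; r = 0.41 at n = 40; r = 0.30 at n = 80), or declare one-sided testing for the directional hypotheses only and give a two-sided figure for resting-state fMRI.
3. For d only, add the range under Holm with the number of tests stated. With seven, it is 0.63 to 0.81 two-sided, or 0.56 to 0.75 one-sided.
4. Note that these are unadjusted t-test figures, and that the planned baseline-adjusted models may do better by an amount that depends on the baseline correlation.
5. Optionally, add a figure for 70 completers (35 per group): two-sided d = 2.842/√(35/2) = 0.68.

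The cost is one reworded paragraph and a less favourable stated sensitivity. The sample size stays at 80, and no participants or procedures are added.

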Connected to others	Connected VAS NIH Toolbox Social Satisfaction Summary BFI-2 Agreeableness BFI-2 Conscientiousness BFI-2 Extraversion
Creative	Creative VAS AUT RAT CAT Everyday problem solving
Focused	Focus VAS
Guilty	Guilt VAS
Happy	Happy VAS NIH Toolbox Psychological Well-Being Summary
Meditative	FFMQ
Motivated	Motivated VAS
Open to new experiences	BFI-2 Open-Mindedness MODTAS State of Surrender (−) State of Preoccupation 5D-ASC
Sad	Sad VAS DASS Depression
Stressed	Stressed VAS PSS DASS Stress
Well	Well VAS (−) AEs Fitbit Sleep and Activity
*Do you expect that microdosing will change how ____ you feel?*	
Craving	Craving VAS
Energy	Energy VAS (−) Tired VAS Fitbit Sleep and Activity
Self-efficacy	NIH Self-Efficacy
*Do you expect that microdosing will affect your ___*	
Cognitive functioning	NIH Toolbox Fluid Cognition Composite Score

“−” indicates negative correlation is expected

An interim analysis will be undertaken at 6-month periods for review by the Data Safety and Monitoring Committee (DSMC; see the “Data and safety monitoring” section). Interim analyses include recruitment and dropout rates, demographics, data completion, attendance and compliance, comparison of outcome measure baseline means by group, summaries of daily mood VAS ratings and vital signs, summaries of adverse events, and comparison of adverse events between the groups (see the “Adverse event reporting and harms” section). The DSMC is able to terminate the trial based on these reports.

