Careful monitoring of expectancy and unmasking will also give insight into the role of placebo effects in full-dose psychedelic experiences. Due to the significant perceptual effects of psychedelics, placebo effects are difficult to parse in full dose trials; however, sub-hallucinogenic microdoses that are carefully monitored for unmasking will provide an opportunity to gain an insight into the magnitude of these effects. Expectancy of the positive effects of microdosing has been demonstrated among those who frequent drug use forums [20], likely inflating the benefits reported by those who learn about microdosing online, and these attitudes have been shown to correlate to positive self-reported outcomes [13], and to potentially explain the difference in outcomes between microdosing and placebo in a self-blinded study of people microdosing in the community [21]. Positive coverage of the practice in local news will potentially be producing a similar effect in the general population from which we are drawing participants. By assessing expectancy at baseline, we will be able to assess the effect of these attitudes on participant outcomes. Expectancy is also likely to change in uncontrollable ways during the trial, as participants may be exposed to information about microdosing and talk to peers about the trial. Efforts need to be made to reduce these occurrences, for example, by keeping participants with concurrent appointments separate from each other and by discouraging participants from conducting online research into microdosing. Efforts will also be made to prevent unmasking and nocebo effects by priming participants with the expectation that they may not feel any immediate effect from the dose. Participants will not be unmasked until the conclusion of the trial, so that they cannot share whether their experiences were due to placebo or an active dose with associates who may also be enrolled in the trial.

Beyond testing the efficacy and safety of the practice on healthy participants, the practical implementation of a home-dosing regimen of a restricted and easily degraded drug is an essential aspect of assessing the feasibility of LSD microdosing as a potential mental health treatment. Analysis of participant adherence and compliance using MDOT will be valuable to the planning of future trials on clinical populations, as well as shaping policy around potential access in clinical settings.

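### The expectancy regression names no baseline term for the measure it analyses, so followed as written its slope mixes any expectancy effect with pre-existing level

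*Protocol article*

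**What the plan says.** The expectancy analysis is given in one sentence of the protocol article, under Statistical analyses and power calculations: "Expectancy effects will be assessed by regression analysis of measure scores to a corresponding construct on a baseline expectancy questionnaire". No covariate, change score or time point is named.

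Nearby text is more specific about baseline:

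- For the arm comparisons: "Questionnaires and creativity tasks will be assessed with linear mixed models with participants modelled as random factors, using baseline measurements as a covariate".
- For the regressions that follow up significant effects, the predictors include "baseline MODTAS scores, change in MODTAS scores, SoS/SoP, and fMRI baseline connectivity of the DMN as predictors", so baseline level and change are named separately there.

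Table 4 pairs each expectancy item with measures. The item stem reads "Do you expect that microdosing will change how ____ you feel", and one row is "Open to new experiences BFI-2 Open-Mindedness MODTAS State of Surrender". The Discussion gives the purpose: "By assessing expectancy at baseline, we will be able to assess the effect of these attitudes on participant outcomes". The Study design section says that the baseline measures are repeated on day 43 and that daily ratings start the evening after the day −6 visit, about a week before the first dose.

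**The concern.** The items ask what the participant expects to change, and the stated purpose is the effect of that expectation. A regression of the score on the item, with nothing else in the model, tests whether expectancy is associated with the level of the score. The two questions coincide only if expectancy is unrelated to where participants started. Randomisation does not secure this, because expectancy is not randomised.

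The difference matters most for measures that vary mainly between people and are fairly stable within them: the BFI-2 scales, MODTAS, FFMQ, AUT, RAT and the NIH composites. If men who are already more open or creative also expect more change, their later scores will correlate with expectancy even if expectancy moved nothing. If low scorers expect the most change, a real effect can be cancelled.

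The article presents its examination of expectancy and unmasking as a feature of the trial, and four of the seven primary measures (BFI-2 open-mindedness, MODTAS, AUT, RAT) are outcomes in Table 4. A slope that reflects prior level could be reported as a placebo or expectancy effect.

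**Working it through.** **The plan's own figures.** The article gives α = 0.05, power 0.8 and detectable correlations of 0.37 (n = 40) and 0.27 (n = 80). With δ = r√n / √(1 − r²) and n − 2 degrees of freedom:

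- n = 80: 0.27 × 8.944 / √(1 − 0.0729) = 2.508. Power is 80.0% one-sided, 69.7% two-sided.
- n = 40: 0.37 × 6.325 / √(1 − 0.1369) = 2.519. Power is 79.6% one-sided, 69.0% two-sided.

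The figures reproduce one-sided; the article does not state sidedness. They describe linear regressions in general and do not settle the expectancy model. Everything below uses a two-sided 5% test, which is an assumption.

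**Model.** Baseline Y0 and expectancy E have SD 1 and correlation c. Follow-up is Y1 = ρY0 + bE + error, with error variance 1 − ρ². From the article: n = 80 (combined) or 40 (one group). Assumed: ρ from 0.5 to 0.8, c from −0.3 to 0.4, b = 0 or 0.2.

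- Y1 on E alone: slope = Cov(Y1, E) / Var(E) = b + ρc.
- Y1 on E and Y0: slope = b.

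**No expectancy effect (b = 0), n = 80.** The correlation of Y1 with E is then ρc, and δ = ρc√80 / √(1 − ρ²c²). Simulated columns use 20,000 runs per cell.

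| ρ | c | ρc | δ | Unadjusted, formula | Unadjusted, simulated | Adjusted, simulated |
|---|---|---|---|---|---|---|
| 0.7 | 0 | 0 | 0 | 5% | 5.1% | 5.1% |
| 0.7 | 0.2 | 0.14 | 1.265 | 23.9% | 24.2% | 5.0% |
| 0.5 | 0.3 | 0.15 | 1.357 | 26.8% | 26.7% | 5.1% |
| 0.7 | 0.3 | 0.21 | 1.921 | 47.5% | 46.9% | 5.2% |
| 0.8 | 0.3 | 0.24 | 2.211 | 58.9% | 57.9% | 4.8% |
| 0.7 | 0.4 | 0.28 | 2.609 | 73.1% | 71.7% | 5.0% |

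**True effect b = 0.2, c = 0, n = 80.** Unadjusted, the residual variance is ρ² + (1 − ρ²) = 1, so δ = 0.2 × 8.944 = 1.789 and power is 42.4% (simulated 41.5–41.7%). Adjusted, δ = 1.789 / √(1 − ρ²):

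- ρ = 0.5: δ = 2.066, power 53.2% (simulated 52.0%)
- ρ = 0.7: δ = 2.505, power 69.6% (simulated 67.7%)
- ρ = 0.8: δ = 2.981, power 83.7% (simulated 81.8%)

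**Both present (b = 0.2, ρ = 0.7, n = 80).**

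- c = −0.3: unadjusted slope 0.2 − 0.21 = −0.01; rejection 5.4%, against 63.7% adjusted.
- c = +0.3: unadjusted slope 0.2 + 0.21 = 0.41; rejection 95.0%, against 63.9% adjusted. The excess is bias, not power.

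**n = 40.** With b = 0 and c = 0.3, false rejection is 15–32% unadjusted against about 5% adjusted. With b = 0.2 and c = 0, power is about 23% against 29–51%.

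**Limits of the remedy.** A change score on its own has slope b − (1 − ρ)c under this model, and at c = 0.3 with b = 0 it rejects in 13–27% of trials (n = 80). If instead expectancy follows the underlying trait, and baseline and follow-up are equally reliable measurements of it, E has correlation c with both. The adjusted partial correlation is then c(1 − ρ) / √((1 − ρ²)(1 − c²)). At c = 0.3 this is 0.06 / (0.6 × 0.954) = 0.105 for ρ = 0.8 and 0.09 / (0.714 × 0.954) = 0.132 for ρ = 0.7. In simulations with arm in the model (2,000 runs per cell, n = 80), false rejection was 15–22% adjusted and 4–6% for the change score; unadjusted it was about 79% at ρ = 0.8. Neither remedy is exact in both settings, which is why the two should be reported together.

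**The case against.** The strongest reply is that the article is silent rather than wrong. It does not call the scores raw, fix the time point or rule out a baseline covariate. It condenses a fuller protocol, and an analysis plan not shown may list covariates. The sentence names no arm term either, so silence alone cannot prove a deliberate exclusion. The separate mention of baseline and change in MODTAS concerns predictors, and the baseline covariate stated for the questionnaire models might have been meant to carry over. This stands as far as intent goes: a reader might infer that the authors chose to leave baseline out, and the text does not show that. What remains is that the article states a model for this analysis, and that model does not match the purpose stated for it.

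Other points also stand:

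- A reader might conclude that the regression detects trait differences instead of change. It carries both, as b + ρc, and is unbiased when c = 0.
- Loss of power is not general. When b and c share a sign, rejection rises, although through bias.
- Most Table 4 measures are not stable traits. Of about 40, 15 are VAS mood items, and others are state, adverse-event or activity measures.
- The document gives no correlation between expectancy and baseline, so the size of any bias is unknown.
- The Objectives section states no expectancy hypothesis, the framework is exploratory, and most Table 4 measures are secondary and uncorrected.

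**Conclusion.** The concern holds in this form: the expectancy regression names no own-baseline term and, followed as written, confounds an expectancy effect with any existing link between expectancy and the level of the measure. At n = 80, with ρ assumed between 0.5 and 0.8, the consequences range from lost precision when c = 0 (about 42% power against 52–82% for b = 0.2) to 27–58% false rejection when c = 0.3 and b = 0. The adjusted rate of about 5% applies if expectancy tracks the observed baseline; it is higher if expectancy tracks the underlying trait. ρ, b, c and the two-sided test are all assumptions.

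The exposure is greatest for the trait and ability measures. It bears on how expectancy findings are interpreted in a supportive, largely exploratory analysis. A reader might extend it to the efficacy results, but the arm comparisons are separate models, and those for questionnaires and creativity tasks are stated "using baseline measurements as a covariate". They are not affected.

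**What to change.** Replace the sentence with: *Expectancy effects will be assessed by regressing the post-baseline score on the corresponding expectancy item, adjusting for arm and, where one exists, the baseline value of the same measure (the pre-dose-week mean for daily VAS items), with a change-score regression as sensitivity analysis. For measures without a pre-dose value, the unadjusted regression will be reported as an association.*

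Which measures fall in the last group depends on the assessment schedule, whose figure is not shown; 5D-ASC is a likely candidate.

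No new data are needed, since the baseline battery and a week of pre-dose daily ratings are already collected. The cost is one degree of freedom per model for the baseline term (and one for arm), plus some residual bias from measurement error in the baseline. Disagreement between the adjusted and change-score results would help to reveal that bias. If a fuller analysis plan already contains this adjustment, the article's sentence only needs to be aligned with it.
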